## SAP Revision History

| Version | Reason(s) for change                                                                                                                                                                                                                                                                                                                                                                                                                                              | Date        |
|---------|-------------------------------------------------------------------------------------------------------------------------------------------------------------------------------------------------------------------------------------------------------------------------------------------------------------------------------------------------------------------------------------------------------------------------------------------------------------------|-------------|
| 1.0     | Original                                                                                                                                                                                                                                                                                                                                                                                                                                                          | 21-JUL-2023 |
| 2.0     | Specified pre-defined analyses, reconfigured dummy tables, added data dictionary.                                                                                                                                                                                                                                                                                                                                                                                 | 14-NOV-2023 |
| 3.0     | Added post hoc analyses of comparative performance of HemoCue and SD Biosensor haemoglobin measurements following anecdotal evidence of some seemingly erratic SD Biosensor haemoglobin results                                                                                                                                                                                                                                                            | 7-FEB-2024  |
| 4.0     | Added table for post hoc analyses of comparative performance of HemoCue and SD Biosensor haemoglobin measurements in Appendix 2 and 3                                                                                                                                                                                                                                                                                                                      | 27-FEB-2024 |
| 5.0     | Updated Stage 2 power and precision calculations given change in predicted patient recruitment in Stage 2                                                                                                                                                                                                                                                                                                                                                         | 21-JUN-2024 |
| 6.0     | Updated Stage 2 power calculations for detection of a reduction in incidence due to an error found in initial calculation. Also provide power calculations for detection of individual-level reduction in risk of recurrence in Stage 2.

Two additional analyses added to assess the association between haemoglobin and G6PD activity, and the additional exploratory endpoint, methaemoglobin levels on days 3 and 7.                                    | 23-OCT-2024 |
| 7.0     | Added dummy Table S1a for protocol violations in Stage 2 in appendix 3                                                                                                                                                                                                                                                                                                                                                                                            | 10-FEB-2025 |
| 8.0     | Added to Section11:

i) exploratory analyses for a new Stage 2 effectiveness endpoint (S2.SE18) - cumulative risk of representation to the same health facility with symptomatic P. vivax malaria within 6 months of patients enrolled and not enrolled in SCOPE in post-implementation stages.                                                                                                                                                      | 07-JUL-2025 |
| 9.0     | -deletion of exploratory analysis for haemoglobin change (S2.EE1 absolute & S2.EE2 proportional in the first 3 days) as haemoglobin data only routinely collected at baseline in Stage 2.

-addition of subgroup of Sumatra compared to PNG & Indonesian Papua.

-sensitivity analysis of S2.SE15 changed from pre-implementation period of 3 years (data not available across all clinics) to including only incidence data from previous 12 months. | 11-NOV-2025 |

|  |                                                                                                                                                                                                                                                                                                                                                                                                                                                                                                                                                                                                                                                                                                                                                                              |  |
|--|------------------------------------------------------------------------------------------------------------------------------------------------------------------------------------------------------------------------------------------------------------------------------------------------------------------------------------------------------------------------------------------------------------------------------------------------------------------------------------------------------------------------------------------------------------------------------------------------------------------------------------------------------------------------------------------------------------------------------------------------------------------------------|--|
|  | 
-sensitivity analysis added which includes the stage 1 data in the post-implementation period for S2.SE15.
 
-S2.SE15 – analysis models for both level and slope change previously had indicator variables marking the pre- and post-implementation periods differently. These have been made uniform, so that estimates are based on the same set of assumptions.
 
-addition of sensitivity analysis for S2.SE18 for Indonesian sites, including only patients with a malaria card number.
 
-addition of clarifying detail for S2.SE18; propensity scores only to be used when an imbalance in baseline characteristics exists, deletion of subgroup analysis for patients <30% G6PD activity, addition of stage 1 data in SCOPE-enrolled group.
 |  |
|--|------------------------------------------------------------------------------------------------------------------------------------------------------------------------------------------------------------------------------------------------------------------------------------------------------------------------------------------------------------------------------------------------------------------------------------------------------------------------------------------------------------------------------------------------------------------------------------------------------------------------------------------------------------------------------------------------------------------------------------------------------------------------------|--|

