## 7 Outcomes and Covariates

The primary, secondary and exploratory outcomes for Stage 1 and Stage 2 are defined in Section 2.2 (Endpoints).

Intervention and covariate variables for analyses of the impact of the implementation package on incidence of symptomatic *P. vivax* malaria (effectiveness outcome S2.SE15) will be defined as follows:

- a) **Level change** intervention effect (i.e. change in mean monthly incidence) 6 months after the start of stage 2; Figure 2, Section 9.
- b) **Slope change** intervention effect (i.e. change in the rate of change of monthly incidence) immediately after the start of stage 2; Figure 2, Section 9.

Intervention will take the value of 1 for all time points following the start of stage 2 implementation at each health facility site, and a value of 0 for all other timepoints for both the level and slope changes.

The time month covariate will be defined as the number of months after the start of stage 2 implementation (Appendix 4: Figure 1), i.e. negative values for pre-implementation and positive values for post-implementation.

Seasonality will be captured using spline terms for the Indonesian health facility sites and the PNG health facility sites.

Any unexpected stock outages or major, discrete malaria control interventions external to the SCOPE project will also be captured and reported by health facility site and calendar time month.

The key covariates that will be included in the analyses of the safety and exploratory outcomes will be the haemoglobin concentration at enrolment, the mg/kg dose of primaquine and the G6PD enzyme activity. Key covariates to be adjusted for in the analysis of patient-level effectiveness outcomes will be baseline age, weight and sex, except in the case that these variables have already been considered in a propensity score matching process.

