### Dataset for Analysis

Endpoint S2.SE18 will include all SCOPE patients eligible for PQ treatment and a selected dataset of non-SCOPE patients who were treated with PQ treatment for *P. vivax* malaria according to national guidelines. SCOPE patients from both stage 1 and stage 2 will be included. The non-SCOPE patients will be eligible for selection if they were not enrolled in SCOPE at any stage (based on malaria card number and other identifying factors) and were administered the PQ dose according to national guidelines and met the SCOPE eligibility criteria: age >1 year (PNG) or ≥6 months (Indonesia, haemoglobin concentration ≥8 g/dl, and not pregnant or lactating and did not have severe malaria. Day 0 for non-SCOPE patients will be taken as the first visit by a patient following the stage 1 implementation date.

In the scenario that the baseline characteristics differ substantially between the SCOPE and non-SCOPE patients, a subgroup of these non-SCOPE patients will be selected for analysis using propensity score matching with the SCOPE patients. This will be done separately by country (PNG and Indonesia) and will be based on the following variables:- age, sex, body weight. Propensity score matching is a valuable way to control for bias and achieve pseudo randomisation in this exploratory analysis which is comparing SCOPE patients to routinely collected patient data.

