### Statistical Analysis

A flowchart will be provided for the non-SCOPE patients, presenting the number of patient data available, eligible/non-eligible for selection, the reason for being non-eligible, and if applicable, the numbers selected/not-selected based on propensity score matching with SCOPE patients.

The number (proportion) of SCOPE patients and non-enrolled patients (if applicable ‘propensity-score matched (PSM) selected’) will be presented stratified by country and health facility. The distribution of age, sex, body weight and primaquine dose will be presented in a Table for SCOPE patients (enrolled in post-implementation stage), and non-enrolled eligible patients (and if applicable, non-enrolled PSM-selected patients) to assess the balance of the distribution of age, sex and body weight.

If applicable, to determine the PSM selected patient dataset, the propensity score for SCOPE versus non-SCOPE eligible patients will be estimated using logistic regression with covariates age, sex, and body weight. This regression analysis will be conducted separately by country. We will then use the estimated propensity scores from each of these analyses separately for matching without replacement ‘m’ non-enrolled eligible patients to each SCOPE patient based on a distance that corresponds to ≤0.2 standard deviations of the estimated log odds of the estimated propensity score.

The risk that patients represent with *P. vivax* malaria within 6 months to the same health facility site (S2.SE18) will be analysed using survival analysis and visualised with Kaplan-Meier curves. The risk of recurrence will be determined for all SCOPE patients eligible for PQ treatment and non-SCOPE patients (and if applicable non-SCOPE PSM selected patients) administered PQ treatment. Multivariable Cox proportional hazards regression will be used to compare the SCOPE and non-SCOPE patients in the post-implementation period, controlling for calendar time at first visit (month) and seasonality (captured using splines) and a shared frailty of health facility. The validity of the proportional hazards assumption will be assessed visually using Schoenfeld residuals and stratified analyses will be conducted where the assumption is violated.

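### S2.SE18 leaves recent P. vivax history out of every covariate list and chooses between matched and unmatched analysis by an undefined imbalance in age, sex and body weight

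*SAP*

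**What the plan says.** The SAP's revision history gives the version 9.0 rule for S2.SE18: "propensity scores only to be used when an imbalance in baseline characteristics exists". Section 11 carries it out.

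- **Trigger.** Matching begins with the condition "In the scenario that the baseline characteristics differ substantially between the SCOPE and non-SCOPE patients". No threshold is given. The planned table also shows primaquine dose, but its stated purpose is "to assess the balance of the distribution of age, sex and body weight".
- **Score.** Matching is done by country and "will be based on the following variables:- age, sex, body weight". The score "will be estimated using logistic regression with covariates age, sex, and body weight".
- **General Cox model.** It compares the two groups "controlling for calendar time at first visit (month) and seasonality (captured using splines) and a shared frailty of health facility". Section 7 requires age, weight and sex in patient-level effectiveness models, "except in the case that these variables have already been considered in a propensity score matching process".
- **Unmatched option.** The last paragraph of Section 11 lists age, sex and body weight with facility frailty. It does not mention calendar month or season.
- **Time zero.** "Day 0 for non-SCOPE patients will be taken as the first visit by a patient following the stage 1 implementation date". These patients must also never have enrolled in SCOPE. Section 11 sets no corresponding first-visit rule for SCOPE patients, who come from both stages.

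Previous P. vivax episodes are not a covariate in Section 7 or Section 11.

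**The concern.** The outcome is another P. vivax presentation, and Section 4.2.1 attributes 60% of clinic cases to relapse. A recent episode is therefore an obvious candidate predictor of the next one. Section 11 describes matching as a route to pseudo-randomisation, but matching on age, sex and weight cannot balance visit history.

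The Day 0 rule makes an imbalance plausible. If the first visit means the first P. vivax visit, a non-SCOPE patient whose Day 0 falls more than six months after the Stage 1 date has no recorded P. vivax visit in the preceding six months, by definition. A SCOPE patient may enrol at a later visit and carry such a history. The balance check does not look at history, so it cannot detect the difference.

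The trigger is a separate problem. The branch taken changes the sample, the covariates and the population to which the estimate applies. As written, it may also change whether calendar time and season are adjusted for. With no threshold, two analysts could take different branches on the same data.

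**Working it through.** **1. Reference effect.** S2.SE18 has no target effect or power figure. The only recurrence hazard ratios with stated power are in Table 3 of Section 4.2.1, for S2.SE17. Inputs from that section: 20% risk at six months, 10% loss, alpha 0.05 (taken as two-sided), 11,410 patients per period.

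- Rates per six months: recurrence −ln(0.8) = 0.2231; loss −ln(0.9) = 0.1054.
- Event probability = rate/(rate + loss) × (1 − exp(−(rate + loss))). This gives 0.190 in the reference group and 0.173 at HR 0.9.
- Events = 11,410 × (0.190 + 0.173) ≈ 4,144 with unrounded probabilities.
- Schoenfeld power: √(4,144/4) × |ln 0.9| − 1.96 = 3.39 − 1.96 = 1.43, that is 92.4%. The plan states 92%, so Table 3 reproduces.

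**2. Bias from an omitted binary covariate.** Let p1 and p0 be the shares with recent P. vivax in SCOPE and non-SCOPE patients, and H its recurrence hazard ratio. The factor on the estimated HR is approximately (1 + p1(H − 1)) / (1 + p0(H − 1)). The SAP gives none of the three, so the values below are assumptions. First case: p1 = 30%, p0 = 15%.

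| H | Factor | True 0.90 reads | True 0.70 reads |
|---|---|---|---|
| 1.5 | 1.15/1.075 = 1.07 | 0.96 | 0.75 |
| 2.0 | 1.30/1.15 = 1.13 | 1.02 | 0.79 |
| 2.5 | 1.45/1.225 = 1.18 | 1.07 | 0.83 |

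With the shares reversed (15% and 30%) the factors invert to 1.075/1.15 = 0.93, 1.15/1.30 = 0.88 and 1.225/1.45 = 0.84. A package with no effect would then appear beneficial.

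**3. What it takes to mimic each effect.** Set p0 = 40% and no true effect. A spurious 0.90 needs p1 = 26% at H = 2 (0.90 × 1.40 = 1.26). A spurious 0.70 is impossible at H = 2, where the lowest possible factor is 1/1.40 = 0.71. At H = 3 it needs p1 = 13% (0.70 × 1.80 = 1.26).

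**4. Check by simulation.** Cox models were fitted to 60,000 simulated patients per group with 20% risk, 10% loss, H = 2 and a true HR of 1.0. With history in 20% of SCOPE and 40% of non-SCOPE patients, the HR was 0.87 without the covariate and 1.02 with it. With shares of 40% and 20% it was 1.16 and 1.00.

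**The case against.** Much stands on the other side. A reader might infer that confounding is handled by age, sex and weight alone. It is not: the score is fitted by country, non-SCOPE patients must meet SCOPE eligibility and have had guideline primaquine, facility frailty is in both options, and the general model has calendar month and season. The unmatched paragraph may be meant to add to that model, though it does not say so. Nor are the three covariates left uncontrolled without matching, since the Cox model then adjusts for them. The trigger looks at baseline data, not outcomes. Section 10 adds an analysis restricted to Indonesian patients with a malaria card, aimed at differing health-seeking.

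A reader might also infer that the bias equals the effect sought. The documents do not support that. No target is set for S2.SE18, and the inputs and direction are assumed. At the 30% versus 15% shares used here, a true HR of 0.70 still reads as a benefit.

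It is tempting to subtract 11,410 from 16,300, take 4,890 as the comparator size, and argue that a trivial difference would trigger matching by a p-value. But 16,300 derives from annual episodes rather than distinct patients, the SCOPE group also includes Stage 1, and Section 11 names no significance test.

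Finally, the SAP does not say that prior-visit histories already exist. That they can be derived is an inference. S2.SE17 needs individual re-presentation data from before implementation, and Section 3.1 reports more than 12 months of surveillance at eight of the ten sites. Linkage will be weaker for patients without a card.

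**Conclusion.** The concern holds in limited form. Three features of the text are certain: no covariate for recent P. vivax, no definition of a substantial difference, and no repeat of the calendar and seasonal terms in the unmatched option. That visit history differs between the groups is likely under the Day 0 rule, but depends on whether first visit means first P. vivax visit.

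The size and direction of the bias are unknown. Under the assumed 30% versus 15% and hazard ratios of 1.5 to 2.5, the shift is a factor of 1.07 to 1.18. That is enough to hide most or all of a 10% reduction, the smallest effect in a table written for S2.SE17. It is not enough to hide the predicted 30% reduction in relapse risk, read as HR 0.70; producing a spurious effect of that size needs an extreme imbalance. Section 11's exploratory label limits the consequence, but the listing among secondary endpoints means the result will probably be reported beside S2.SE17.

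**What to change.** Prespecify one primary S2.SE18 analysis with no trigger: a Cox model in all eligible SCOPE and non-SCOPE patients. Always adjust it for age, sex, body weight, recorded P. vivax visits at the facility in the six months before Day 0 (with an unknown level), calendar month, seasonality and facility frailty. Report standardised differences, including prior visits. Keep propensity matching as a sensitivity analysis, with prior visits in the score.

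Because the Day 0 rule forces a zero count for many non-SCOPE patients if first visit means first P. vivax visit, adjustment alone may extrapolate. Add a sensitivity analysis restricted, in both groups, to patients with no recorded P. vivax visit in the look-back.

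Do not carry the covariate into S2.SE17. Visits after implementation may already reflect the package, so adjusting for them could remove part of its effect.

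The cost is SAP wording and one derived variable. The look-back will be incomplete at sites with recent surveillance (North Sumatra, Lampung) and for patients without a malaria card. The covariate also does not remove selection from requiring non-SCOPE patients never to have enrolled, which should be stated as a limitation.

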**LIST OF ACRONYMS**

| Acronym | Definition                                                      |
|----------------|------------------------------------------------------------------------|
| ACT            | Artemisinin-based Combination Therapy                                  |
| ADL            | Activity of Daily Living                                               |
| AE             | Adverse Event                                                          |
| AESI           | Adverse Event of Special Interest                                      |
| AMM            | Adjusted Male Median                                                   |
| ANZCTR         | Australian New Zealand Clinical Trials Registry                        |
| BRIN           | Badan Riset dan Inovasi Nasional (Indonesia)                    |
| CHW            | Community Health Worker                                                |
| CI             | Confidence Interval                                                    |
| CQI            | Continuous Quality Improvement                                         |
| DFAT           | Department of Foreign Affairs and Trade (Australia)                    |
| FDA            | Food and Drug Administration                                           |
| FGD            | Focus Group Discussion                                                 |
| G6PD           | Glucose-6-Phosphate Dehydrogenase                                      |
| G6PDd          | G6PD deficiency                                                        |
| GI             | Gastrointestinal Intolerance                                           |
| GST            | Global Study Team                                                      |
| HCP            | Healthcare Provider                                                    |
| MoH            | Ministry of Health                                                     |
| NDA            | National Drug Authority                                                |
| NDoH           | National Department of Health                                          |
| NMCP           | National Malaria Control Program                                       |
| PCR            | Polymerase Chain Reaction                                              |
| PNG            | Papua New Guinea                                                       |
| PQ             | Primaquine                                                             |
| PQ7            | Primaquine 1.0 mg/kg/day for 7 days                                    |
| PQ14           | Primaquine 0.5 mg/kg/day for 14 days                                   |
| PQ8W           | Primaquine 0.75mg/kg/week for 8 weeks                                  |
| RDT            | Rapid Diagnostic Test                                                  |
| SAE            | Serious Adverse Event                                                  |
| SCOPE          | Short Course Primaquine for the radical cure of P. vivax |
| SMC            | Safety Monitoring Committee                                            |
| SRT            | Safety Review Team                                                     |

YPKMP

*Yayasan Pengembangan Kesehatan dan Masyarakat Papua*  
(Papua Health and Community Development Foundation)

